### Study Objectives

#### Primary Objectives

The primary objectives of this study are as follows:

To improve current predictive models or develop new predictive models for placental dysfunction–related pregnancy complications, including preterm preeclampsia and FGR, at 2 critical gestational periods: the first trimester (11‐13 weeks) and the second trimester (26‐28 weeks)To establish third-trimester (35‐36 weeks) models to predict term preeclampsia and FGR and to define the optimal time for delivery.

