### Definitions of Preeclampsia and FGR

The diagnosis of preeclampsia follows the 2021 International Society for the Study of Hypertension in Pregnancy guideline [31]. Preeclampsia cases are subclassified based on gestational age at delivery as preterm preeclampsia (delivery <37 weeks) or term preeclampsia (delivery ≥37 weeks) [31]. FGR is defined in the absence of congenital anomalies according to international Delphi consensus criteria, with distinctions between early-onset and late-onset presentations (Textbox 1) [32].

Textbox 1.Definitions of early- and late-onset fetal growth restriction [32].

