#### Sample Size Estimation

We estimate a 10% to 15% participation rate from the approximately 5000 annual deliveries at GCUH. On the basis of a prevalence of 10% for placental dysfunction–related disorders (preeclampsia and SGA or FGR), approximately 200 cases with these outcomes are expected. In the development of prediction models using binary outcomes (high-risk or low-risk) with a 10% incidence rate and up to 15 predictors, targeting an area under the receiver operating characteristic curve (AUC-ROC) of 0.75, the estimated sample size is approximately 1700 participants [42].

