#### Primary Objectives: Prediction Model Development

Multivariable logistic regression will serve as the primary analytical approach for prediction model development at 3 gestational windows (11‐13 weeks, 26‐28 weeks, and 35‐36 weeks of gestation) to address both primary objectives 1 and 2. Clinically relevant candidate predictors are predefined and entered into multivariable models, followed by model reduction to achieve parsimony (eg, backward elimination with a retention threshold of *P*<.10). Nonlinear relationships between continuous variables and the log odds of the outcomes will be tested with the inclusion of polynomial terms up to the third degree, which will be kept in the model if statistically significant.

For each patient, this method estimates a predicted probability of developing the outcome based on the log odds of the outcome. For primary objective 1, the predicted probabilities can be used to define low- and high-risk subgroups at predefined gestational age thresholds. Specifically, a risk threshold will be defined based on clinically relevant screen-positive rates (eg, 10%, 15%, or 20%) to balance sensitivity and specificity for clinical implementation. For primary objective 2, logistic regression will similarly provide predicted probabilities. In addition, Fine and Gray competing risks time-to-event models will be used as sensitivity analyses accounting for delivery without the outcome of interest (preeclampsia or FGR) as a competing event.

To further improve upon current FMF prediction models, a Bayesian updating approach will be applied to refine existing FMF first-trimester risk estimates using additional biomarkers and clinical variables collected later in pregnancy. The FMF first-trimester risk estimate will be used as the prior probability. Likelihood ratios derived from biomarker and biophysical measurements at 26 to 28 weeks and 35 to 36 weeks will be incorporated via Markov chain Monte Carlo simulations to generate updated posterior risk distributions. This enables dynamic, individualized risk reassessment as pregnancy progresses.

All models will undergo internal validation using 5-fold cross-validation with repeated iterations to obtain stable performance estimates. Model performance will be evaluated using the following metrics:

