## Discussion

This protocol describes a prospective cohort study aimed at developing advanced prediction models for placental dysfunction–related pregnancy complications, allowing for dynamic and personalized accurate risk assessment throughout the pregnancy. First- and second-trimester prediction models aim to enhance early risk assessment for placental dysfunction–related complications (preeclampsia, FGR, preterm birth, and stillbirth), and the third-trimester model focuses on predicting the onset of term complications (preeclampsia and FGR) and determining optimal delivery timing. This comprehensive strategy advances personalized obstetric care through evidence-based risk stratification.

The FMF first-trimester prediction model shows superior performance compared with traditional risk-factor–based checklists [17]. By combining maternal factors with measurements of MAP, UtAPI, and serum PlGF, this model is the most effective method for predicting early-onset and preterm preeclampsia, achieving detection rates of 90% and 75%, respectively [22,43]. This model has been validated across diverse populations, consistently demonstrating predictive performance comparable to the original studies and has been tested in randomized clinical trials [24,44-48]. Importantly, when coupled with prophylactic low-dose aspirin administration starting before 16 weeks’ gestation in high-risk pregnancies, this screening strategy reduces preterm preeclampsia by more than 60% [24,49]. In addition, the model achieves detection rates of 56% for early SGA fetuses (<32 weeks) and 46% for preterm SGA neonates (<10th percentile), with aspirin use potentially reducing the incidence of preterm SGA by 20% and early SGA by 40% [23].

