This project aims to enhance existing prediction models for term preeclampsia and SGA through the evaluation of additional biomarkers across 3 critical gestational stages, investigating both routine antenatal measurements and specialized markers of placental and cardiovascular dysfunction, including Doppler ultrasound parameters, maternal hemodynamic indices, and angiogenic markers. Doppler ultrasound assessment of uterine arteries can reflect placental perfusion status, with elevated values indicating increased resistance and impaired placental blood flow [57,58]. Maternal hemodynamic parameters, including ophthalmic artery Doppler indices, MAP, and augmentation index, provide insights into cardiovascular adaptation and peripheral vascular function [59-61]. Angiogenic markers (sFlt-1, PlGF, and the sFlt-1:PlGF ratio) indicating angiogenic imbalances serve as biochemical predictors of placental dysfunction [20,62,63] and spontaneous preterm labor [64]. Furthermore, our study establishes a valuable biobank for identifying novel molecular biomarkers and investigating underlying mechanisms of placental dysfunction through omics techniques. Incorporating these diverse markers and novel biomarker candidates into existing prediction models has the potential to enhance accuracy for late-onset pregnancy complications.

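### The models are to predict FGR, but the expected case count and sample size rest on a broader pool that includes SGA, which the study never defines

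*Protocol article*

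**What the plan says.** Most of the article fixes the fetal outcome as FGR.

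- **Primary Objectives.** The first objective covers complications "including preterm preeclampsia and FGR, at 2 critical gestational periods". The second is to establish third-trimester "models to predict term preeclampsia and FGR and to define the optimal time for delivery".
- **Definitions of Preeclampsia and FGR.** "FGR is defined in the absence of congenital anomalies according to international Delphi consensus criteria". Textbox 1 then lists antenatal size and Doppler criteria, separately for early and late onset.
- **Primary Objectives: Prediction Model Development.** The Fine and Gray sensitivity analysis treats "delivery without the outcome of interest (preeclampsia or FGR) as a competing event".
- **Discussion, opening paragraph.** The third-trimester model is described as addressing preeclampsia and FGR.

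Two places differ.

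- **Sample Size Estimation.** At a 10% prevalence of placental dysfunction–related "disorders (preeclampsia and SGA or FGR), approximately 200 cases with these outcomes are expected". The same paragraph uses a 10% incidence, up to 15 predictors and a target AUC of 0.75 to arrive at about 1700 participants.
- **Discussion, paragraph on additional biomarkers.** "This project aims to enhance existing prediction models for term preeclampsia and SGA".

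The only threshold attached to SGA is in the account of the existing Fetal Medicine Foundation (FMF) model, which is credited with detecting "46% for preterm SGA neonates (<10th percentile"). Nothing in the Methods defines SGA as an outcome of this study.

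**The concern.** A prediction model needs one defined event, and its sample size has to rest on how often that event occurs. Here the models are for FGR, while the planning rate is for a pool that adds SGA and preeclampsia. If FGR alone is rarer than the pool, the cohort yields fewer events per FGR model than the article implies and supports fewer candidate predictors before overfitting becomes a problem. Separately, a reader of the Discussion could expect an SGA model that the Methods do not specify. Birth weight is collected (Table 1), so such a model could be fitted and then confused with the FGR one.

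**Working it through.** **1. Are the two labels interchangeable under the article's own criteria?** No, in either direction.

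- *Small but not FGR.* At 32 weeks or later, a fetus with abdominal circumference or estimated weight between the 3rd and 10th percentile, and no other criterion, meets one of the three contributory items. Two are needed, so it is not FGR.
- *FGR but not below the 10th percentile.* At 32 weeks or later, centile crossing plus an abnormal cerebroplacental ratio or umbilical artery index meets two of the three items with no size cut-off.
- *Different measurement.* FGR is scored on antenatal scans. The one SGA threshold in the article refers to neonates.

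**2. Reproduce the stated size.** Inputs from Sample Size Estimation: incidence 10%, P = 15 predictors, AUC 0.75. Assumption: global shrinkage S = 0.90, which the article does not state.

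- The AUC was converted to a Cox-Snell R² by simulating a normal linear predictor with cases shifted by √2·Φ⁻¹(0.75) SD (2,000,000 records). At 10% incidence, R² = 0.0757.
- Formula: n = P / [(S − 1)·ln(1 − R²/S)].
- n = 15 / [−0.10 × ln(1 − 0.0757/0.90)] ≈ 1,707, against about 1700 stated. A repeat simulation gave about 1,720.
- The companion criteria need less: 596 for optimism in R² and 138 for precision of the overall risk.
- S matters: 0.85 gives 1,072 and 0.95 gives 3,612. Only 0.90 comes near the stated figure.

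The stated size is therefore consistent with a 10% event rate, the same rate the paragraph gives for the pooled disorders.

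**3. Change only the incidence.** AUC, P and S stay as above. The rates below 10% are assumptions, because the article gives no FGR-only rate.

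| Incidence | R² | Required n |
|---|---|---|
| 10% (stated, pooled) | 0.0757 | 1,707 |
| 7% (assumed) | 0.0557 | 2,349 |
| 5% (assumed) | 0.0415 | 3,181 |
| 3% (assumed) | 0.0258 | 5,148 |

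**4. What the enrolled cohort would support.** Results reports 1267 enrolled, of whom 1072 + 144 = 1216 have completed or are still to complete their pregnancy. For fixed S and R², n is proportional to P, so the supported P is 15 × 1216 / n.

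- 10%: 0.10 × 1216 ≈ 122 events; 15 × 1216/1,707 = 10.7 predictors.
- 5%: 0.05 × 1216 ≈ 61 events; 15 × 1216/3,181 = 5.7 predictors.
- 3%: 0.03 × 1216 ≈ 36 events; 15 × 1216/5,148 = 3.5 predictors.

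These are upper limits for any one gestational window, since women may join at any stage before 37 weeks and not all will have data at every visit.

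**5. Side note.** At 10%, 1700 participants give 170 cases; 200 cases would need 200/0.10 = 2000 participants. The point here does not depend on which of the two is meant.

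**The case against.** The best reply is that the text governing the analysis is consistent. Objectives, definitions, Textbox 1 and the competing-risks outcome all say FGR, and SGA is given neither a definition nor a model in the Methods. On this view the Discussion sentence merely carries over the label of the existing FMF models, whose performance the article reports as SGA detection rates, and the case count is a rough planning figure.

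Much of that stands, and it rules out several stronger readings.

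- *That SGA is the project's stated aim.* It appears in one Discussion sentence. The abstract's objective, the Introduction's aim and the primary objectives do not name it, and the Discussion's own opening says FGR.
- *That the fetal outcome is left open to be chosen after results are seen.* The operative passages fix FGR, so two stray labels do not show this.
- *That SGA and FGR pick out mostly different babies.* The article gives neither rate nor their overlap. If SGA were 10% and every FGR baby were also SGA, the shared fraction would be 30%, 50% or 70% at FGR rates of 3%, 5% or 7%. Simulating the overlap needs an assumed correlation between scan and birth size, and a model using estimated weight alone would omit abdominal circumference and the centile-crossing-plus-Doppler route.
- *That SGA or FGR alone must exceed 10%.* This follows only if SGA is set at 10% to begin with, so it shows no error in the planning rate.

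What the reply does not answer is the sample-size paragraph. That paragraph is in the Methods, its rate is tied explicitly to the pooled label, and the stated size depends on that rate.

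**Conclusion.** The point holds as an inconsistency with a consequence for sample size. The fetal outcome is FGR wherever the analysis is specified, SGA or FGR pooled with preeclampsia where cases are counted, and SGA in one aim sentence. SGA is undefined as a study outcome and differs from FGR under Textbox 1. The 10% incidence, the roughly 200 cases and the 1700 participants therefore do not carry over to a model of FGR alone.

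The size of the effect depends on an FGR-only rate that the article does not give. The range of about 3,200 participants at 5% to about 5,100 at 3% is illustrative and rests on an assumed shrinkage of 0.90, the stated AUC of 0.75 and all 15 predictors. The direction is firm: an FGR rate below the pooled 10% requires more participants or fewer predictors. With 1267 enrolled and recruitment closed, only the number of predictors, or the precision claimed, can still be adjusted.

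**What to change.** 1. Keep Delphi FGR as the fetal outcome of the primary models, as the objectives and definitions already have it.
2. Replace SGA with FGR in the Discussion's aim sentence and in the case count under Sample Size Estimation.
3. In that section, state the expected number of FGR events with the rate assumed and its source, and give the number of candidate predictors, or the precision, that the enrolled cohort supports for that outcome.
4. If SGA is to be reported, name it as a separate secondary outcome derived from the birth weight already collected, with its own definition.

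The cost is wording in two places and one recalculation; no new data are needed. The downside is that the stated event count and the supported model size will look less favourable than they do now.
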